**Methods:**

Patients meeting set criteria will be sequentially enrolled up to a sample size of 40. Twenty patients who meet the inclusion criteria for controls will also be evaluated. Patients will be examined by a qualified phonoaudiologist who will take biometric measurements and administer the Expanded Protocol of Orofacial Myofunctional Evaluation with Scores (OMES), Friedman Staging System, Epworth Sleepiness Scale, and Pittsburgh Sleep Quality Index questionnaires. Measures of upper airway muscle tone will also be performed using the Iowa Oral Performance Instrument and tongue digital spoon devices. Evaluation will be recorded and reevaluated by a second specialist to determine concordance between observers.

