However, it is currently unknown which patients are the best candidates for myofunctional therapy. Although there are instruments available for patient selection such as the Expanded Protocol of Orofacial Myofunctional Evaluation with Scores (OMES), involving functional exploration of all of the stomatognathic functions to obtain a score, this has proven to be inferior in patients with OSAHS compared with controls [16,17]. A myofunctional therapist uses this evaluation to improve the examined items that are in deficit and subsequently performs specific exercises to improve them. However, the OMES test is based on subjective evaluations, contains many items, and is difficult to reproduce. In our opinion, a more concise, objective, and reproducible evaluation is required. This opinion stems from our experience of measurements with the Iowa Oral Performance Instrument (IOPI) of the genioglossus muscle and the orbicular muscle [18,19]. Together with measurement of the motor tone of the genioglossus muscle using a tongue digital spoon (TDS) [20], these simple measurements may provide patients with information about their condition, serve as therapy response parameters, and objectively transmit results between professionals, which can also be based in electronic health facilities [21].

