### Sample Size and Sampling Procedure

The effectiveness of use of the OMES protocol in the evaluation of patients with moderate to severe apnea-hypopnea syndrome will be evaluated from data previously published in studies using this protocol. Following the literature review, patients will be recruited. The sample size will be 60 subjects (40 in the experimental group and 20 in the control group). The sample size was calculated using the XLSTAT statistical software for Excel.

The variables that we are going to measure in all patients are reflected in the data collection table shown in Multimedia Appendix 1 using SPSS Info software, including age, sex, weight, height, ethnicity, BMI, abdominal circumference (at the level of the navel), neck circumference (using a flexible tape around the most prominent part while the patient is standing with their arms by their sides, head erect, and eyes looking ahead), IOPI measurement of tongue strength and the buccinator muscle, AHI, nighttime oxygen desaturation index, lowest overnight oxygen saturation levels, digital spoon measurement of tongue strength, and OMES protocol.

A series of questionnaires will be applied to both groups: Friedman Staging System, Epworth Sleepiness Scale, and Pittsburgh Sleep Quality Index (see Multimedia Appendix 2). An information sheet and information consent will also be provided and signed by patients.

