#### IOPI Evaluation

The IOPI objectively measures maximum tongue and lip strength. Tongue strength is assessed by measuring the maximum pressure exerted when a person presses a disposable, standard-sized tongue bulb against the roof of the mouth. Lip strength is assessed by measuring the maximum pressure when the bulb is located between the cheek and closed teeth, and the patient contracts the buccinator muscle without biting the bulb. Reference values have been obtained for a healthy population and are provided by the manufacturer [18].

Tongue strength is measured by obtaining maximal tongue elevation pressures. The patient is instructed to “place this bulb in your mouth on the midline of your tongue and push it against the roof of your mouth as hard as you can.” To maximize standard placement, the examiner demonstrates how to place the bulb along the central groove of the tongue blade. Previous research [18] indicates that maximal measures of tongue strength and endurance are best assessed with an unconstrained jaw; participants will be encouraged to gently rest the incisors on the tubing of the IOPI bulb. Each test lasts 7-10 seconds, and all participants will be given verbal encouragement from the examiner for the entire test. The test will be performed three times by each participant, with a brief rest of about 30 seconds between each test while the examiner records the peak pressure obtained. The highest pressure across the three trials will be used as the maximal isometric pressure instead of the mean pressure, which has been used by other researchers [22]. Given the high correlation between the average and maximal pressure and that both are similarly related to oral-phase swallowing function, the use of maximal pressure is more efficient in a clinical setting because it requires no calculation.

Subsequently, the muscle tone of the genioglossus muscle and the buccinator muscle are evaluated, taking three measurements of each and using the highest value.

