#### TDS Evaluation

Finally, the tone of the tongue muscles will be measured with a digital spoon, taking three measurements and using the highest obtained. A digital spoon is a kitchen tool used to estimate the weight of food. To develop the TDS, we used the Soehnle Cooking Star Digital Measuring Spoon with graduation from 0.1 grams to 500 grams (ID ID20005876833). This is a handheld instrument with a spoon that can be found on online shopping platforms, consisting of a handle where the “tare” and “hold” buttons are located. Pressing the “hold” button helps to obtain the highest tared value, equivalent to the IOPI peak pressure. To carry out the measurements, the spoon is inverted and a 1-cm^2^ circular sticker is placed on the back to obtain a marked circumference. To measure tongue strength, the subject holds the spoon by the handle and, with their elbow resting on a flat surface, brings the spoon closer to the tongue with an elbow angle of approximately 30°. The subject must then tare the device by pressing the “hold” key, marking 0.0 grams. The subject then presses on the marked circumference with the tip of their tongue. Once done, with the index finger of the hand that is holding the handle, the subject presses the “hold” button. This test is performed entirely by the subject to avoid movements on the spoon that may interfere with the results [20].

The recordings and the data obtained will also be analyzed by another blinded examiner.

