### Statistical Analysis

The data of the study variables will be collected in a database created for the development of the study. In the statistical analysis, the sample will be described through the distribution of frequencies for the categorical variables, and through measures of central tendency and dispersion such as the mean (SD) and median (IQR) for quantitative variables. The distribution of quantitative variables will be examined using the Kolmogorov-Smirnov test. Bivariate analysis of the association between categorical variables will be carried out using the χ^2^ test or Fisher exact test when necessary. The differences between quantitative variables will be analyzed using the Student *t* test or analysis of variance for two or more samples, respectively, and nonparametric tests (Mann-Whitney or Kruskal-Wallis test) will be used if the variables to be analyzed do not follow the normal distribution. The possible correlations between the OMES protocol evaluation and the IOPI values and TDS will be assessed using the Spearman rank correlation coefficient. The consistency and stability of the intra- and interrater measurements (reliability coefficient) will be determined using the split-half method. The level of statistical significance will be set at *P*<.05.

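### The split-half method planned for rater reliability does not measure the agreement between observers that the second rating is meant to establish

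*Protocol article*

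**What the plan says.** The Abstract (Methods) gives the purpose of the second rating: "Evaluation will be recorded and reevaluated by a second specialist to determine concordance between observers". The TDS Evaluation section repeats the arrangement: "The recordings and the data obtained will also be analyzed by another blinded examiner". The Statistical Analysis section names one method for the resulting data: "The consistency and stability of the intra- and interrater measurements (reliability coefficient) will be determined using the split-half method". The article names no ICC, kappa or limits of agreement, and it does not say whether items, trials or raters are to be split.

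Two further statements bear on the point. The Background section says of the rated instrument that "the OMES test is based on subjective evaluations, contains many items, and is difficult to reproduce". The IOPI Evaluation section describes "taking three measurements of each and using the highest value", and the TDS Evaluation section likewise takes three readings and keeps the highest.

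**The concern.** Split-half reliability asks whether two halves of one measurement rank subjects alike. Observer concordance asks whether two people scoring the same subject arrive at the same score. The first can be high when the second is poor, and the reverse is also possible.

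The rater analysis is the only one in the article that bears directly on its criticism that OMES is hard to reproduce. With the planned coefficient, the study could report a poorly reproducible score as reliable, or a well-agreed score as unreliable, and a reader could not tell which had happened.

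**Working it through.** The plan gives no reliability coefficient, target or precision, so there is no figure of its own to reproduce. From the article come the two raters and the 60 subjects (40 cases, 20 controls). Every correlation, offset and variance below is an assumption, used to show how the coefficient behaves.

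**Reading A: the two raters are the halves.** Let r be the inter-rater correlation and b the systematic offset between raters in within-rater SDs, with equal variances.

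- Split-half after Spearman-Brown: 2r / (1 + r)
- Single-rater absolute-agreement ICC: r / (1 + b²/2)

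For r = 0.60, split-half is 1.20 / 1.60 = 0.75. The ICC is 0.60 with b = 0, 0.60 / 1.125 = 0.53 with b = 0.5, and 0.60 / 1.5 = 0.40 with b = 1.

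| r | Split-half | ICC, b = 0 | ICC, b = 0.5 | ICC, b = 1 |
|---|---|---|---|---|
| 0.50 | 0.67 | 0.50 | 0.44 | 0.33 |
| 0.60 | 0.75 | 0.60 | 0.53 | 0.40 |
| 0.70 | 0.82 | 0.70 | 0.62 | 0.47 |
| 0.90 | 0.95 | 0.90 | 0.80 | 0.60 |

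On this reading the coefficient exceeds single-rater agreement for every r between 0 and 1, because it describes the sum of two ratings and b does not enter it. The excess is small when r is high and there is no offset (0.95 against 0.90), and large with a 1 SD offset (0.95 against 0.60).

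**Reading B: one rater's items are split.** Take k = 20 items and subject variance S = 1. H is the variance of a rater-specific error common to all of that rater's items for a subject. V is true subject-by-item variation seen by both raters. E is independent item noise, and b is the offset on the scale where S = 1.

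- Correlation of the half-scores: (S + H) / (S + H + 2(V + E)/k)
- After step-up: (S + H) / (S + H + (V + E)/k)
- ICC between raters: (S + V/k) / (S + H + (V + E)/k + b²/2)

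| H | V | E | b | Split-half | ICC between raters |
|---|---|---|---|---|---|
| 1 | 0 | 1 | 0 | 2/2.05 = 0.98 | 1/2.05 = 0.49 |
| 1 | 0 | 1 | 1 | 2/2.05 = 0.98 | 1/2.55 = 0.39 |
| 0.25 | 0 | 1 | 0 | 1.25/1.30 = 0.96 | 1/1.30 = 0.77 |
| 0 | 0 | 1 | 1 | 1/1.05 = 0.95 | 1/1.55 = 0.65 |
| 0 | 0 | 1 | 0 | 1/1.05 = 0.95 | 1/1.05 = 0.95 |
| 0 | 9 | 0.25 | 0 | 1/1.4625 = 0.68 | 1.45/1.4625 = 0.99 |
| 0.04 | 16 | 0.25 | 0 | 1.04/1.8525 = 0.56 | 1.80/1.8525 = 0.97 |

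Simulation of every row but the fifth (60 subjects, 1,000 runs each) agrees to within 0.02. The formulas show why the two quantities part. Split-half counts a rater's private error H as reliability and ignores b. It counts genuine item differences V as unreliability, although both raters see them. The second rater appears nowhere in it.

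**Intra-rater part.** The sentence also promises intra-rater reliability. The article describes a one-off visit and a second analysis by a different examiner, and no second scoring by the same rater. The three IOPI and TDS trials are repeat efforts by the subject. Agreement across them is within-subject repeatability and says nothing about raters.

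**The case against.** The strongest reply is that little depends on this coefficient. Reliability is not among the main or secondary objectives, and neither the case-control comparisons nor the Spearman correlations use it. The recordings and second ratings will exist whatever the sentence says, so agreement can be computed at analysis without touching the design. The Background remark on OMES is context, and the article's answer to it is the two devices, not a reliability study of OMES. All of this stands and limits the severity.

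A second reply is that an article condenses a fuller plan. That would excuse an omitted method. Here a method is named, and it does not serve its stated purpose.

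A third reply is that the coefficient may come out about right. It can: with purely independent item noise the two quantities coincide (fifth row under reading B), and with raters as halves, high correlation and no offset they are close. These are special conditions, and split-half cannot show whether they hold.

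A reader might infer that the reported reliability will probably be far too favourable. The documents do not support this. They give no rating data and do not say what is split, and the large upward gaps under reading B come from assuming a rater-wide error or an offset. OMES covers appearance and posture, mobility, respiration, deglutition and mastication, so heterogeneous items are plausible and could push an item split below true agreement. A reader might also think that IOPI and TDS offer only one reading each. In fact three are taken, and only the analysed value is single.

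**Conclusion.** The point holds as a wrong choice of method: split-half, on either reading, does not estimate the concordance between observers that the Abstract promises. If raters are the halves, the error is upward; for an assumed correlation of 0.60 the report would be 0.75 against agreement of 0.40 to 0.60 for offsets from 1 SD down to none. If items are split, the assumed settings give anything from 0.98 against 0.39 to 0.56 against 0.97. These figures illustrate the mechanism and are not estimates for this study, because the variance components and the offset are assumed. Severity is should-fix, confined to the reliability result. A reader should not infer that the comparison of cases with controls is compromised.

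**What to change.** Replace the split-half sentence as follows.

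- **Inter-rater:** for OMES total and domain scores, a two-way, absolute-agreement, single-rater ICC with 95% CI between the live and the video examiner, with Bland-Altman bias and limits of agreement. Use weighted kappa for ordinal items. Report within cases as well as pooled, since pooling raises the ICC if cases and controls differ on the score.
- **Intra-rater:** either delete the claim, or have the same rater rescore existing recordings and apply the same statistics.
- **IOPI and TDS:** describe agreement across the three trials as within-subject repeatability, not as rater agreement.

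The inter-rater change costs one sentence and a few lines of analysis syntax, with no new data. The intra-rater option costs rescoring time. The article reports 20% of the planned sample collected, so the method can be settled before analysis. The drawback is that the reported coefficient may be lower. Precision should be usable: with 60 subjects, two raters and an assumed ICC of 0.80, the 95% CI is about 0.69 to 0.88. It will be wider within the 40 cases.

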### Ethical Aspects

The Research Ethics Committee of the Hospital Provincial de Málaga reviewed and approved the protocol and the informed consent model for the patients (AWGAP-2021-02). Before performing any of the procedures specified in the study protocol, the participating subjects will have signed and dated the informed consent form approved by the Research Ethics Committee.

### Access to Data and Protection of Data Obtained from the Study

To guarantee the confidentiality of the study data, the original data will be stored at the hospital and only researchers and the Research Ethics Committee will have access.

This project will be carried out following the guidelines of the Declaration of Helsinki (Fortaleza, Brazil, 2013) [23] and the Standards of Good Clinical Practice. Personal data will be processed according to Regulation (EU) 2016/679 of the European Parliament and of the Council (April 27, 2016) on the protection of natural persons with regard to the processing of personal data and on the free movement of such data, and Organic Law 3 (December 5, 2018) on the protection of personal data and guarantee of digital rights.

### Usefulness and Applicability

The selection criteria for patients with OSAHS may improve depending on which therapy is more suitable.

## Results

The authors plan to publish the study findings in a peer-reviewed journal and at topic-related conferences (to be determined at a later date). All listed authors or contributors are compliant with guidelines outlined by the International Committee of Medical Journal Editors for author inclusion in a published work. Furthermore, to support research transparency and reproducibility, we will share the deidentified research data after publication of the study results. We will also share the deidentified data on Figshare, a repository where users can make all of their research outputs available in a citable, shareable, and discoverable manner. To date, we have collected data for 20% of the planned sample. The timeline for data collection to completion of the study is given in Figure 2.

**Figure 2 figure2:**
[figure not shown]
Summary of the results.

## Discussion

### Projected Significance

Although Eckert [24] proposed that one of the phenotypes responsible for initiating sleep apnea is the hypotonic pattern in 2016, studies have yet to be performed to confirm this proposal. It is well known that patients with this phenotype can benefit from treatment with a hypoglossal pacemaker, myotonic medication such as desipramine, and myofunctional therapy. We consider that our study will help to identify certain patients with severe OSAHS according to distinct anthropometric and myofunctional features from those of conventional patients (ie, individuals with obesity or with anatomical issues such as big tonsils). Following our experience using the IOPI [18], we consider that patients with a normal BMI, neck and bell circumference, and anatomy of the upper airway will show no relationship with the position of the tongue or the soft palate. We previously demonstrated that Friedman stage is independent from the tone of the muscle of the genioglossus as measured by the IOPI [18].

The patients’ main anomaly will be determined by their responses to the OMES questionnaire, and with the measures of the upper airway muscles using the IOPI and TDS.

The TDS is a simple, reproducible, and affordable method to measure the muscle tone of the tongue for this patient group. We have pioneered the use of this domestic tool to allow patients to obtain immediate feedback of their success in performing myofunctional therapy exercises. In our opinion, the OMES questionnaire is a suitable tool to make a diagnosis for these patients, but can only be performed by specialized phonoaudiologists and requires considerable time. In most countries, there is a lack of phonoaudiologists and the demand on their time means that consultations are short. We contend that we can provide this information with the assistance of the IOPI and TDS that do not require any special training.

The information provided by these two instruments can be correlated with the information obtained by the OMES. In this case, these two measures are fast, simple, reproducible, and provide objective information to both the patient and examiner.

### Limitations

One of the limitations of this study is that although we are going to identify patients according to their singular characteristics, we are not going to be able to demonstrate the effectiveness of the exercises performed with myofunctional therapy. Theoretically, these patients should improve with myofunctional therapy, a hypoglossal pacemaker, or inotropic medication. We intend to perform that study as a continuation of this proposed trial.

Our main concern is that if these patients have myofunctional disorders (ie, low OMES, IOPI, or TDS scores), the therapist is obliged to correct the deficits simultaneously with the use of CPAP. We are strongly opposed to any surgery in patients where there is a demonstrated myofunctional disorder.

### Comparison With Prior Work

No previous work directed at this matter has been performed for effective comparison.

### Conclusions

This study will help determine the muscle patterns in patients with severe OSAHS and may be used to fill the current gap in the identification of patients suitable to be treated with myofunctional therapy.

## Appendix

Multimedia Appendix 1 PowerPoint presentation with database.

Multimedia Appendix 2 Information sheets; informed consent; and Pittsburg, Friedman, and Epworth questionnaires.

Multimedia Appendix 3 OMES questionnaire.

## Abbreviations

AHI: Apnea-Hypopnea Index
CPAP: continuous positive airway pressure
IOPI: Iowa Oral Performance Instrument
MAD: mandibular advancement device.
OMES: Orofacial Myofunctional Evaluation with Scores
OSAHS: obstructive sleep apnea-hypopnea syndrome.
TDS: tongue digital spoon
